### **9.3.3. Microbiological Samples and Testing\***

#### **Respiratory Culture, Gram Stain and Sensitivity Testing**

Respiratory specimens should be obtained within 24 hours before the first dose of study drug. In the event that a subject has received nonstudy antibiotics before study enrollment, respiratory cultures obtained before, or as soon as possible, but within 24 hours after the start of nonstudy antibiotic treatment must be available. This culture must be repeated, if necessary, so that a respiratory specimen is collected within 24 hours before the first dose of study drug. All procedures should be performed according to local best practice. Specimens obtained by deep expectoration or nasotracheal aspiration are only acceptable in nonventilated subjects. Suitable specimens from expectorated samples are defined as having <10 squamous epithelial cells and >25 leukocytes per low powered field (LPF) (10x objective). In a Gram stain, an organism is considered predominant if there are >10 organisms per oil-immersion field in 10 fields (100x objective). Suitable specimens for ventilated subjects include bronchoscopy with BAL/protected-brush sampling, or transtracheal/endotracheal aspiration at baseline for Gram stain, culture, and sensitivity testing. Where possible, invasive specimens (BAL or protected-brush sampling) with quantitative cultures should be obtained on all ventilated subjects.

In all cases of clinical failure, new cultures must be attempted, with susceptibility testing on isolated pathogens.

---

\* This section of the protocol has been revised. Please refer to the section of this document entitled PROTOCOL AMENDMENTS (Amendment INT-3, 22 December 2006) for a detailed description of the specific changes.

If a primary isolate was unsuccessfully transferred to the central laboratory, the local laboratory results may be considered as definitive.

See Attachment 3, Procedure for Collection, Culture, Susceptibility Testing, Storage, and Shipment of Microbiological Samples.

### **Blood Cultures**

At least 2 sets of aerobic/anaerobic blood cultures must be obtained according to local practice for each subject, within 24 hours before the start of treatment. In the event that a subject has received nonstudy antibiotics before study enrollment, blood cultures obtained before, or as soon as possible, but within 24 hours after the start of nonstudy antibiotic treatment must be available. These cultures must be repeated, if necessary, so that a blood culture is collected within 24 hours before the first dose of study drug. At least 1 culture should be taken from a peripheral vein. Cultures must either be drawn one after the other from different sites or drawn from the same site, 10 minutes apart. Any potential pathogen should be stored and shipped to the central laboratory.

Positive blood cultures at baseline or follow-up (concordant growth of the same pathogen in at least 2 bottles or corresponding to a respiratory isolate) must be repeated at each visit or more frequently, if indicated, until negative cultures are obtained. If blood cultures on 3 consecutive days are positive, the subject should be withdrawn from the study and considered a treatment failure. If negative blood cultures are obtained at baseline, blood cultures should be repeated at subsequent visits only if clinically indicated. Culture procedures will be according to local practice.

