- g At the investigator’s discretion, therapy may be stopped anytime after the fifth day of therapy when the infection is considered clinically cured (based on normalization of the clinical signs and symptoms of infection and improvement in the chest X-ray and after a minimum of 5 total treatment days).
- h If treatment has been extended to 10 days, and it is determined that the subject needs additional antibiotics, the assessments should be performed and any significant findings discussed with the Medical Monitor. If the subject does not need additional antibiotics, the EOT assessment should be performed.
- i End-of-treatment (EOT) assessments must be performed within 48 hours after the end of therapy.
- j If a subject withdraws prematurely, TOC/early termination visit procedures must be completed at time of withdrawal.
- k Late follow-up by telephone contact unless an examination is needed to evaluate relapse (need for further antibiotic treatment) or abnormalities at TOC assessment.
- l The results of the *legionella* urine antigen test should be available within 24 hours after enrollment. Subjects with proven *legionella* infection should be discontinued from the study and treated appropriately.
- m Women of childbearing potential only. Pregnancy testing will be performed by serum or urine according to local regulations. Additional serum or urine pregnancy tests will be conducted throughout the study in sufficient number, as determined by the investigator or according to local regulations, to establish the absence of pregnancy during the study.
- n The pharmacist will be unblinded to prepare appropriate dosing. An unblinded monitor will perform drug accountability.
- o To include temperature, pulse, respiratory rate, and blood pressure and must be done twice daily at least 8 hours apart, while hospitalized. The vital signs that reflect the highest temperature recorded for the subject on that day should be captured in the case report form (CRF).
- p To be measured at the discretion of the investigator, (e.g., clinically relevant abnormalities, findings, or values or to evaluate relapse).
- q Only clinically significant changes in abnormalities from previous assessment should be recorded.

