## 9.3. Efficacy Evaluations

### 9.3.1. Clinical Efficacy Assessments

Clinical assessments will be done during the study after review of the inclusion/exclusion criteria and documented informed consent has been obtained.

---

\* This section of the protocol has been revised. Please refer to the section of this document entitled PROTOCOL AMENDMENTS (Amendment INT-3, 22 December 2006) for a detailed description of the specific changes.

JNJ-30982081: Clinical Protocol 30982081-CAP-3001 - Amendment INT-3

At the baseline (Day 1) assessment, the following clinical signs and symptoms will be reported as present or absent:

- Cough
- Production of purulent sputum or respiratory secretions
- Presence of rales or evidence of pulmonary consolidation on chest auscultation
- Rigors or shaking chills
- Pleuritic chest pain
- Tachypnea
- Hypoxemia

At all subsequent assessments, changes in signs and symptoms will be reported in comparison with the baseline (Day 1) assessment as:

- Worsened from baseline visit
- Unchanged from baseline visit
- Improved from baseline visit
- Absent

Overall clinical assessment will be compared with the baseline (Day 1) visit:

- Worsened from baseline visit
- Unchanged from baseline visit
- Improved from baseline visit
- Cured

At the TOC assessment, the clinical outcome will be rated as follows:

**Cure:** resolution of signs and symptoms of the infection (return to pre-infection baseline), or improvement to such an extent that no further antimicrobial therapy is necessary and improvement or stabilization of chest X-ray findings.

**Failure:** death due to pneumonia occurring more than 48 hours after first infusion or a lack of efficacy (incomplete resolution of signs and symptoms of the infection, i.e., remains worse than pre-infection baseline or worsening of the chest X-ray) and requirement for additional nonstudy antibiotics to treat this episode of pneumonia after at least 48 hours of study therapy.

***Unable to evaluate:*** Discontinued early (before completing full course of study antibiotic) for any reason other than lack of efficacy and requires further antibiotics.

Subjects, who have missing data from the TOC visit, will be considered clinical failures, if they are worsened or unchanged from baseline at the EOT visit, provided that they meet no other criteria for nonevaluability.

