## **10. SUBJECT COMPLETION/WITHDRAWAL**

### **10.1. Completion**

A subject will be considered as having completed the study if he/she has completed all assessments at the LFU visit and received at least 5 days of study treatment. Subjects who discontinue study treatment after 48 hours of treatment due to lack of efficacy are also considered to have completed the study.

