### **10.2. Discontinuation of Treatment**

A subject should be discontinued from study treatment if:

- the investigator believes that for safety reasons (e.g., adverse event) it is in the best interest of the subject to stop treatment
- the subject becomes pregnant
- creatinine clearance is <10 mL/min or the subject requires dialysis
- significant myelosuppression occurs during therapy with linezolid/placebo; treatment with linezolid/placebo should be stopped unless it is considered absolutely necessary to continue therapy, in which case, intensive monitoring of blood counts and appropriate management strategies should be implemented
- optic or peripheral neuropathy occurs during therapy with linezolid/placebo; treatment with linezolid/placebo should be stopped

unless it is considered absolutely necessary to continue therapy. Optic and peripheral neuropathy are potential adverse effects of linezolid therapy. Subjects will be educated on symptoms associated with optic neuropathy (e.g., acute blurred vision, vision loss, color loss) and peripheral neuropathy (e.g., paresthesia, sensory loss) and instructed to report them if they occur. If subjects report symptoms of visual impairment, such as changes in visual acuity, changes in color vision, blurred vision, or visual field defect, prompt ophthalmic evaluation is recommended. Visual function should be monitored in all subjects reporting new visual symptoms, regardless of the length of linezolid therapy. Subjects with significant or progressive symptoms will be discontinued from linezolid/placebo therapy and referred for specialty evaluation if symptoms persist.

If a subject discontinues treatment early, TOC assessments should be performed at the time of study drug discontinuation. The subject should be contacted at the LFU visit to obtain MRU information and to follow up on any ongoing adverse events.

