### **10.3. Withdrawal From the Study**

A subject will be withdrawn from the study for any of the following reasons:

- lost to follow-up
- withdrawal of consent (subjects who withdraw consent should be treated appropriately).

In case a subject is lost to follow-up, every possible effort must be made by the study site personnel to contact the subject and determine the reason for discontinuation. The measures taken to follow up must be documented.

When a subject withdraws before completing the study, the reason for withdrawal is to be documented on the CRF and in the source document. Study drug assigned to the withdrawn subject may not be assigned to another subject. Subjects who withdraw will not be replaced.

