## **11.3. Analyses Methods\***

### **11.3.1. Definition of Populations**

The following subject populations will be defined for the analyses:

Intent-to-Treat (ITT) Population: The set of all randomized subjects.

Modified Intent-to-Treat (mITT) Population: The subset of randomized subjects with a confirmed pathogen in baseline samples.

Clinically Evaluable (CE) Population: The subset of the ITT population who received at least 1 dose of study drug, excluding those subjects with a clinical outcome of Unable to Evaluate at the TOC visit and who have <5 days of study treatment. Those who have at least 2 days of treatment but who are judged as clinical failures will be evaluable.

Microbiologically Evaluable (ME) Population: All randomized subjects who received at least 1 dose of study drug with a confirmed pathogen in baseline sample, excluding those subjects with a microbiological outcome of Unable to Evaluate at the TOC visit.

Safety Population: All randomized subjects who are exposed to study drug.

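### The three-day positive blood culture rule in Section 9.3.3 takes subjects out of the study rather than off study drug, so deaths in the 30-day mortality endpoint could be missed

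*Protocol*

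**What the plan says.** The rule stands in Protocol Section 9.3.3, Blood Cultures: "If blood cultures on 3 consecutive days are positive, the subject should be withdrawn from the study and considered a treatment failure". No other current section repeats it. These parts of the protocol bear on it:

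- **Section 10.1, Completion:** "Subjects who discontinue study treatment after 48 hours of treatment due to lack of efficacy are also considered to have completed the study".
- **Section 10.2, Discontinuation of Treatment:** lists reasons for stopping study drug; uncleared bacteremia is not among them. After an early stop, TOC assessments are done at once, and then: "The subject should be contacted at the LFU visit to obtain MRU information and to follow up on any ongoing adverse events".
- **Section 10.3, Withdrawal From the Study:** "A subject will be withdrawn from the study for any of the following reasons". Two reasons follow, loss to follow-up and withdrawn consent.
- **Time and Events Schedule, footnote j:** "If a subject withdraws prematurely, TOC/early termination visit procedures must be completed at time of withdrawal". The End-of-Treatment Visit text in Section 9.1.4 says the same. Neither states any later contact.
- **Section 9.3.3, Urine Antigen Testing:** mycoplasma and chlamydia titers are to be repeated at LFU in treatment failures.
- **Sections 9.4 and 11.3.5:** pneumonia deaths within 30 days of randomization are a secondary endpoint, compared between arms by Fisher's exact test.

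**The concern.** The protocol keeps two exits apart. A subject who stops study drug (Section 10.2) is still contacted at LFU. A subject who leaves the study has TOC procedures on leaving, and nothing further is stated. The blood culture rule uses the language of the second exit for a subject who, by the logic of Section 10.1, belongs to the first.

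The group matters for mortality. These subjects have not cleared bacteremia on study drug, and Section 1.2 says bacteremia raises mortality about threefold. Clearance is itself a response to treatment, so loss of follow-up need not be equal between arms. If observation ends at the TOC/early termination procedures, a later pneumonia death inside the 30-day window may never reach the database. No analysis plan can restore survival status that was not collected.

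**Working it through.** The protocol gives no figure to reproduce here. The check compares the texts and then sizes the consequence.

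**1. Is the rule consistent with the rest of the protocol?**

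| Place | Status of a subject stopped for non-response | Contact after the stop |
|---|---|---|
| 9.3.3, Blood Cultures | Withdrawn, treatment failure | None stated |
| 10.1 | Completed, if after 48 hours | Not addressed |
| 10.2 | Stopped treatment (trigger not listed) | LFU, for resource use and ongoing adverse events |
| 10.3 | Not a listed reason for withdrawal | None stated |
| 9.3.3, Urine Antigen Testing | Treatment failure | LFU, for titers |

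The withdrawal wording agrees with neither 10.1 nor 10.3, and it works against the LFU titers required later in the same section.

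**2. How much of the 30-day window could go unobserved?** The protocol does not fix the timing. Cultures are repeated at each visit or more often, and inpatients are seen daily.

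- Early case (assumption): the third positive draw is on Day 3 or Day 4, and the result takes 1 to 2 days. Section 9.3.2 mentions overnight and 48-hour reports. With Day 1 as randomization and first dose, withdrawal falls on Day 4 to Day 6, which is 3 to 5 days after randomization. Unobserved: 30 − 5 = 25 to 30 − 3 = 27 days.
- Late case (assumption): withdrawal on Day 14, the longest treatment allowed, which is 13 days after randomization. Unobserved: 30 − 13 = 17 days.

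**3. Would the planned LFU contact close the gap?** LFU is 28 to 35 days after the last dose.

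- Early case: 3 + 28 = 31 to 5 + 35 = 40 days after randomization.
- Late case: 13 + 28 = 41 to 13 + 35 = 48 days.

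In both cases one contact falls after day 30 and can cover the whole window, provided survival is asked about.

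**4. Size per missed death.** 670 randomized 1:1 gives 670/2 = 335 per arm. One missed death changes that arm's rate by 1/335 = 0.30 percentage point.

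**5. Effect on the Fisher test (illustration with assumed counts).** Take equal known deaths in both arms of 335, plus k further deaths unrecorded in one arm. The recorded comparison gives p = 1.00. The comparison with complete data would give:

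| Known deaths per arm | k = 3 | k = 7 | k = 10 |
|---|---|---|---|
| 7 (2.1%) | 0.63 | 0.18 | 0.06 |
| 17 (5.1%) | 0.74 | 0.33 | 0.16 |

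A few unrecorded deaths change little. About ten in one arm could matter, which is more than a rare trigger is likely to produce.

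**The case against.** The strongest reply is that the phrase is loose and that sites would treat these subjects as treatment discontinuations. Pregnancy (Section 12.2.3) and very low creatinine clearance (Section 6.1.4) are also worded as leaving the study, yet both appear in the Section 10.2 list. A subject under the culture rule also stops study drug early, so Section 10.2 can be read to apply, with LFU contact. This has force and makes complete loss of follow-up less likely. It does not settle the matter: unlike those two triggers, this one is missing from the 10.2 list, and the 10.2 contact does not ask about survival.

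Safety reporting is a second backstop. Section 12.2.2 has unresolved serious events followed and treats the cause of a death as a serious adverse event. But Section 12.2.1 does not count disease progression as an adverse event, and after the subject's participation ends it relies on spontaneous reports. That protection is partial.

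The survival gap at LFU is also not peculiar to this rule, since the 10.2 contact is the same for every early discontinuation. That is correct. This rule stands out because it selects subjects on response and, read literally, removes even that contact.

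Three stronger inferences are tempting, and the documents do not support them.

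- **That the primary endpoint is exposed.** Failure in Section 9.3.1 has no culture criterion. Apart from pneumonia death, it needs lack of efficacy "and requirement for additional nonstudy antibiotics to treat this episode of pneumonia after at least 48 hours of study therapy". A reader might therefore place these subjects under Unable to evaluate ("Discontinued early (before completing full course of study antibiotic) for any reason other than lack of efficacy and requires further antibiotics") and then outside the clinically evaluable (CE) population ("excluding those subjects with a clinical outcome of Unable to Evaluate at the TOC visit and who have <5 days of study treatment"). But Section 9.3.3 itself declares them failures, so the stop is not for a reason other than lack of efficacy. Section 11.3.1 keeps failures with at least 2 days of treatment evaluable, and Section 11.3.4 counts missing or non-evaluable outcomes as failures in the intent-to-treat (ITT) population.
- **That the LFU clinical outcome is lost.** Section 9.3.1 carries a TOC failure forward to LFU, and clinical relapse concerns only subjects cured at TOC.
- **That the 14-day extension for persistent bacteremia contradicts the rule.** The extension is permissive and the three-day rule is the more specific instruction, so they overlap without a strict conflict.

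**Conclusion.** The point holds as an inconsistency in a conduct rule, with a possible effect on one tested secondary endpoint. Followed literally, Section 9.3.3 ends observation of a response-defined, high-risk group after the TOC/early termination procedures, and 30-day pneumonia deaths in that group could be missed. How many subjects would meet the trigger cannot be estimated from the protocol; the number is probably small. Each missed death is worth about 0.30 percentage point in its arm. The unobserved period of 17 to 27 days rests on the timing assumptions shown and on a site making no further contact.

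The primary conclusion in CE and ITT is not materially affected. This is a cheap improvement worth making, not a threat to the trial's main result.

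**What to change.** 1. In Section 9.3.3, Blood Cultures, replace *withdrawn from the study* with *discontinued from study drug*, and keep the failure classification.
2. Add the trigger to the list in Section 10.2, so that TOC assessments at discontinuation and LFU contact follow without interpretation.
3. State that these subjects remain in follow-up through LFU, with survival status and cause of death recorded to 30 days after randomization.

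The cost is amendment wording and, for a few subjects, the LFU telephone contact already planned in Section 9.1.5 with a survival question added. No new visit or procedure is needed.

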### **Urine Antigen Testing**

At the screening visit, a urine sample must be obtained and *L. pneumophila* antigen testing performed by the local laboratory.

The Binax NOW® Legionella Urinary Antigen Test is an immunochromatographic membrane assay (ICT) to detect *L. pneumophila* serogroup 1 soluble antigen in human urine. It is not technically demanding and requires no specialized laboratory equipment. Using concentrated urine, it has a sensitivity of 70% to 95% for patients with moderate to severe community-acquired Legionnaires' disease. Its purpose in this study is

to quickly rule out *L. pneumophila* as a cause of the subject's pneumonia so they can be discontinued and treated appropriately (the study drug regimens are not effective against *Legionella* spp). Urinary Legionella antigen testing will be performed in all subjects.

A serum blood sample for mycoplasma and *C. pneumoniae* titers will be evaluated at baseline. Follow-up titers will be obtained at the LFU visit for treatment failures.

#### **9.3.4. Assessment of Microbiological Outcome**

In all cases of clinical failure (see Section 9.3.1, Clinical Efficacy Assessments), samples for new cultures must be obtained and all pathogens isolated will be shipped to the central laboratory for re-identification and susceptibility testing.

Based on information provided on the CRF, at the TOC assessment the sponsor will categorize each pathogen isolated from admission culture (respiratory or blood) according to the following information.

**Eradication:** No growth of a potential pathogen from a culture taken at the original site of infection.

**Presumed Eradication:** No culturable material can be obtained from the original site of infection, in the absence of clinical signs or symptoms of infection.

**Colonization:** Growth of a potential pathogen other than the original pathogen from a culture taken at any time after baseline at the original site of infection, in the absence of clinical signs or symptoms of infection.

**Persistence:** Growth of the original pathogen from a culture at the TOC (or early termination) taken at the original site of infection, with/without the presence of clinical signs or symptoms of infection.

**Presumed Persistence:** No culturable material can be obtained from the original site of infection, in the presence of clinical signs or symptoms of infection.

**Superinfection:** Growth of a pathogen other than the original pathogen from a culture taken at any time after baseline at the original site of infection, in the presence of clinical signs or symptoms of infection.

**Unable to evaluate:** Not able to evaluate microbiological outcome because:

- No pathogen identified at baseline, or
- Absence of clinical determination at TOC, or
- Requires further antibiotics for conditions other than CAP, or
- Other (specified by the investigator).

Only microorganisms from valid samples and those generally accepted as pathogens will be considered when determining the microbiological evaluability of a subject. Isolates from invalid samples may be used for resistance development investigations.

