## 2. OBJECTIVES

The primary objective is to demonstrate the noninferiority of ceftobiprole medocaril compared with ceftriaxone with/without linezolid (comparator) with respect to the clinical cure rate in subjects hospitalized with CAP at the TOC visit.

The secondary objectives are:

- To compare the microbiological eradication rate following treatment with ceftobiprole versus the comparator in subjects with hospitalized CAP at the TOC visit
- To compare the clinical cure rate following treatment with ceftobiprole versus the comparator of hospitalized CAP subjects that require mechanical ventilation within the first 48 hours of enrollment
- To compare the microbiological eradication rate following treatment with ceftobiprole versus the comparator of hospitalized CAP subjects that require mechanical ventilation within the first 48 hours of enrollment
- To compare the clinical and microbiological relapse rates following treatment with ceftobiprole versus the comparator in subjects with hospitalized CAP at the late follow-up (LFU) visit

To compare the 30-day pneumonia-specific mortality rates following treatment with ceftobiprole or the comparator of hospitalized CAP subjects

Other objectives are:

- To assess the PKs of ceftobiprole in subjects treated with ceftobiprole
- To collect medical resource utilization (MRU) data that may be used in future economic modeling

Safety/tolerability objectives are:

- To characterize the safety and tolerability of treatment with ceftobiprole in subjects hospitalized with CAP

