#### **Secondary**

- Microbiological eradication rate, defined as the ratio of the number of subjects with microbiological eradication or presumed eradication to the total number of subjects in the population at TOC visit.
- Clinical cure rate following treatment with ceftobiprole versus the comparator of hospitalized CAP subjects that require mechanical ventilation within the first 48 hours of enrollment

---

\* This section of the protocol has been revised. Please refer to the section of this document entitled PROTOCOL AMENDMENTS (Amendment INT-3, 22 December 2006) for a detailed description of the specific changes.

- Microbiological eradication rate following treatment with ceftobiprole versus the comparator of hospitalized CAP subjects that require mechanical ventilation within the first 48 hours of enrollment.
- Clinical and microbiological relapse at LFU visit
- Thirty-day pneumonia-specific mortality rates following treatment with ceftobiprole or the comparator.

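### The microbiological outcome categories score some clinically cured subjects without a specimen as persistence, and leave some subjects who cleared the baseline pathogen outside the eradication numerator

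*Protocol*

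**What the plan says.** Section 2 lists this secondary objective first: "To compare the microbiological eradication rate following treatment with ceftobiprole versus the comparator in subjects with hospitalized CAP at the TOC visit". Section 11.3.2 sets the endpoint up as a proportion, namely "the number of subjects with microbiological eradication or presumed eradication to the total number of subjects in the population at TOC visit". No other category enters the numerator.

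Section 9.3.4 has the sponsor classify each pathogen from the admission culture at TOC. Four of its categories matter here:

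- Eradication is met when the site culture grows no potential pathogen of any kind; the wording is not limited to the organism found at baseline.
- Presumed Eradication needs two things together, expressed as "No culturable material can be obtained from the original site of infection, in the absence of clinical signs or symptoms of infection".
- Presumed Persistence is the mirror image: the subject likewise yields no specimen but still has signs or symptoms.
- Colonization is described as "Growth of a potential pathogen other than the original pathogen from a culture taken at any time after baseline at the original site of infection"; this label applies when the subject is free of signs and symptoms.

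Persistence, by contrast, is worded in terms of the original pathogen.

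Section 9.3.1 gives clinical Cure two routes: full resolution to the pre-infection state, or "improvement to such an extent that no further antimicrobial therapy is necessary". Both also need a chest X-ray that has improved or stabilized. Apart from death due to pneumonia, Failure needs both a lack of efficacy and additional nonstudy antibiotics.

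The Time and Events Schedule (footnote v) makes post-baseline respiratory cultures, including the one at TOC, conditional on a specimen being available. Section 11.3.1 removes only microbiological Unable to Evaluate outcomes, among subjects with a baseline pathogen who were dosed, from the Microbiologically Evaluable population.

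**The concern.** The clinical and microbiological rules draw the line between success and failure in different places. The clinical rule asks whether more antibiotic is needed. The presumed microbiological categories ask only whether signs or symptoms are present. A subject can therefore be a clinical success and a microbiological failure with no culture evidence that the baseline pathogen survived.

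The wording of Eradication has a related problem. The task is to decide what happened to the admission pathogen, but the criterion is failed by growth of a different organism.

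At stake is the interpretation of the eradication rate, both overall and in subjects ventilated within 48 hours of enrollment, where the same categories apply. Section 11.3.5 also plans a cross-tabulation of cure against eradication; the first problem puts discordance into that table by definition.

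**Working it through.** The protocol gives no assumed eradication rate, margin or power for this endpoint, so there is no figure to reproduce. The check follows subjects through the rules.

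**A. Cured, residual sign, no specimen at TOC**

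1. Section 9.3.1: improved, chest X-ray stable, no further antibiotic needed. Outcome: Cure. It is not Failure, because no additional antibiotic is required.
2. Section 9.3.1 records each sign after baseline as worsened, unchanged, improved or absent. A cough recorded as improved is still present.
3. Section 9.3.4: no material and a sign present. Outcome: Presumed Persistence. Neither the clinical outcome nor the need for antibiotics enters the rule.
4. Section 11.3.2: not in the numerator. Section 11.3.1: not removed from the denominator. Result: non-eradication.

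The same subject with a culture showing no growth would be Eradication, so this path applies only when no material is obtained. Because follow-up respiratory cultures depend on a specimen being available, the schedule itself provides for that case.

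**B. Symptom-free, baseline pathogen cleared, a different organism grown at TOC**

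1. Eradication: not met as worded, because a potential pathogen has grown.
2. Presumed Eradication: not met, because material was obtained.
3. Persistence: not met, because the original pathogen did not grow.
4. Colonization: met. It is outside the numerator and stays in the denominator.

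**C. Symptom-free, a different organism grown during treatment, no growth at TOC**

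1. Colonization: met, because it covers any time after baseline.
2. Eradication: met, because the TOC culture shows no growth.
3. No rule says which prevails or whether both may be assigned.

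**Effect on a comparison (illustration)**

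Assume that a fraction f of true eradications is lost equally in both arms. Then the observed rate = true rate x (1 - f), and the observed difference = true difference x (1 - f). With assumed true rates of 80% and 90%, a difference of -10 points:

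| f | Observed rates | Difference |
|---|---|---|
| 5% | 76.0% vs 85.5% | -9.5 points |
| 10% | 72% vs 81% | -9 points |
| 20% | 64% vs 72% | -8 points |
| 30% | 56% vs 63% | -7 points |

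Both f and the true rates are assumptions; the protocol supplies neither.

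**The case against.** **Signs of infection may exclude trivial residue.** The categories refer to signs or symptoms of infection, and a classifier might disregard a slight cough in someone who needs no further treatment. Section 9.3.4 does not say so, and Section 9.3.1 equates incomplete resolution with remaining worse than the pre-infection baseline. It stands that application may vary, which is itself a reason to fix the wording.

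**The path is narrower than it looks.** It needs the absence of culturable material, and baseline blood pathogens can be re-cultured: Section 9.3.3 requires positive blood cultures to be repeated until negative. This stands and limits the reach.

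**Colonization could be an additional label.** Outcomes attach to admission pathogens, and nothing states that the categories are mutually exclusive. A reader might infer that every colonized subject is certainly counted as non-eradication. The text does not support that: case C also meets Eradication. Case B does fall outside on the wording, since Eradication refers to a potential pathogen whereas Persistence names the original one.

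**A symptom-free requirement can be a deliberate conservative choice.** That is fair, and differing from clinical cure is not in itself an error. But the protocol gives no such rationale, and a presumed outcome has no culture evidence of its own.

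**Bias between arms is not shown.** A reader might infer it because the regimens differ in spectrum; for example, Section 1.1 describes ceftobiprole as active against MRSA and ceftriaxone as not. The rules are common to both arms of a double-blind trial, and the protocol gives no colonization figures. Differential bias remains a possibility only.

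**Conclusion.** The concern holds as a defect in the wording of secondary outcome definitions. With no culturable material at TOC, a clinically cured subject with residual signs or symptoms is scored as non-eradication. A symptom-free subject who has cleared the baseline pathogen but grows another organism at TOC falls outside the numerator. For colonization confined to the treatment period, the classification is undetermined.

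The affected outputs are the eradication rates, overall and in ventilated subjects, and the cure-by-eradication table. The coprimary analyses of clinical cure and the sample size do not use these categories.

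The size cannot be determined from the protocol, which does not state how many subjects will lack a TOC specimen, have residual signs or be colonized. If misclassification is equal in both arms, a true difference shrinks modestly, by 1 to 2 points out of 10 when 10% to 20% of eradications are lost. A reader might infer that a drop in the eradication rate could be set against the 10-point margin for clinical cure. It cannot: the drop is a change in the level of a rate, while the margin bounds a difference between arms.

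**What to change.** Amend Section 9.3.4 and carry the change into Section 11.3.2:

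1. For subjects with no culturable material at TOC, assign Presumed Eradication if the TOC clinical outcome is Cure, Presumed Persistence if it is Failure, and Unable to evaluate if the clinical outcome is Unable to evaluate.
2. Define Eradication as absence of the original baseline pathogen from the TOC culture.
3. Record Colonization and Superinfection as additional emergent outcomes that do not displace the outcome for the baseline pathogen.
4. Report documented and presumed eradication separately.

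The fourth item answers the main drawback: in subjects without a specimen, the microbiological outcome will follow the clinical one, which builds agreement into the cure-by-eradication table. Separate reporting lets a reader see how much of the rate rests on cultures.

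The cost is a wording change. The sponsor already assigns the categories from case report form data, so no new assessment is needed. The change should be made before unblinding.
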